## Abstract

**Clinical Trial Registration:**

https://www.isrctn.com/, identifier ISRCTN13301166; https://clinicaltrials.gov/, NCT06865352.

## Introduction

The Italian age standardized incidence rate for acute lymphoblastic leukemia (ALL) in the 0–19 age population is 36.7 cases per million (95% CI 34.2-39.3) while, for acute myeloid leukemia (AML) it is 6.8 cases per million (95% CI 5.6-8.1). These incidence rates correspond to about 400 new diagnoses of pediatric ALL and 100 new diagnoses of pediatric AML per year in Italy. Even though, currently, more than 80% of children with ALL can be cured with conventional first line chemotherapy, 15-20% of children with ALL still present with disease relapse. The majority of relapsing patients are given an HCT after second-line chemotherapy, but only 30-70% can be cured by HCT (1). A subsequent relapse is the most frequent cause of treatment failure. Considering AML, the event-free survival probability for children treated with the AIEOP-AML 2002/01 protocol was 55% for the whole study population and 53% for high-risk patients (2) and leukemia relapse represented the most common cause of treatment failure. The probability of long-term survival for children relapsing after an allogeneic HCT is low: the vast majority die due to disease progression or for the complications of therapies.

Over the last four decades, allogeneic HCT from an HLA-matched donor, either related or unrelated, has been increasingly used to treat patients affected by various malignant or non-malignant disorders, including acute leukemia. However, only 25% of patients have an HLA-identical sibling and fewer than 60% of the remaining patients can be matched with suitable HLA-compatible, unrelated donors. In the absence of an HLA-matched donor, alternative donors, such as HLA-haploidentical relatives, are being increasingly used (3).

A study by The Acute Leukemia and Pediatric Working Parties of the European Society for Blood and Marrow Transplantation (EBMT) showed that the 5-year leukemia-free survival (LFS) for children with ALL, transplanted in complete remission was about 30%, indicating that haplo­HCT is a useful treatment for patients in morphological remission of disease (4). In particular, in the last years, T-cell receptor (TCR)αβ/CD19 cell depletion has emerged as an effective graft manipulation strategy for preventing GVHD in patients lacking HLA–matched donor and in need of an urgent transplant (5). Despite great improvements, leukemia relapse remains the most frequent cause of transplant failure, especially in high-risk patients, and the prognosis for children affected by acute leukemia and transplanted in an advanced disease stage, in the presence of measurable MRD or with unfavorable cytogenetic abnormalities is still poor, and often less that 50%. Further intensification of pre-transplant chemotherapy and conditioning regimen would increase the incidence of treatment-related toxicity and non-relapse mortality. Thus, in the last few years, clinical research has been directed towards the early identification of patients who cannot be cured by conventional treatment and who could benefit from the use of targeted therapy therapies (6–8).

Harnessing the cytotoxicity and targeting the ability of the cellular immune system could improve the efficacy of anticancer therapy. While the use of monoclonal antibodies is now well established in clinical practice, the development of cellular therapies against cancer has been slower, largely because of the complexity of this approach. Among the different forms of cellular immunotherapy, the adoptive transfer of T lymphocytes is the most promising to overcome leukemia resistance to chemotherapy. T cell therapy for solid and hematological tumors has proved to be effective in preventing or treating cancer growth in patients with different diseases such as melanoma, lymphoma, nasopharyngeal carcinoma (9, 10). Despite these results, cancer immunotherapy still has many limitations and obstacles. Most neoplasms can develop a range of immune escape strategies resulting in failure to appropriately present tumor antigens to immunocompetent cells. Other limitations of immunotherapy based on the infusion of T cells are the suboptimal persistence of transferred cells in the patient and the necessity to define the best tumor associated antigens (TAA) for cellular therapy.

In recent years, excellent results have been achieved in the control of relapsed/refractory ALL with the infusion of T lymphocytes genetically modified to express chimeric antigen receptors (CAR) targeting B cell-associated antigens (11–13). The increase in CAR-T cell efficacy, however, has been paralleled by the potential to induce severe adverse events, including cytokine release syndrome, B cell aplasia, and other severe on-target off-tumor toxicities (14). In addition, despite encouraging data on the treatment of B cell precursor ALL, major challenges remain to be overcome to safely apply CAR-T cell therapy to patients with other leukemia subtypes (T cell precursor ALL or AML) (15–17).

The use of autologous T cells may result in disparities in efficiency or yield of the final product, due to the patient’s prior treatment leading also to a manufacturing failure rate (18). This has led over the years to the development of allogeneic and/or ‘off-the-shelf’ CAR-Ts from healthy donors with the aim of providing a readily available therapeutic solution for patients who needed this therapy. CAR-T production using genome-editing as well as non-gene-editing technologies were evaluated. While these technologies have many advantages, they also have limitations due to associated safety risks, including inducing GVHD and rejection. At present, more extensive researches are required for the development of technologies that allow safe administration of allogeneic CAR-Ts while improving their persistence and their efficacy and maintaining a favorable safety profile (19).

The pivotal therapeutic role of immunity against acute leukemia has been revealed by the graft-versus-leukemia (GVL) effect observed following allogeneic HCT. Moreover, circulating leukemia-specific CTLs have been detected in patients with different forms of acute leukemia, and the presence of these specific T-cell responses in peripheral blood and bone marrow samples of leukemia patients has been associated with improved disease control and longer survival (20–23). This body of data suggests that allogeneic or naturally elicited leukemia reactive T cells could have an effect in preventing relapse and improving transplant outcome.

Unmanipulated donor lymphocyte infusion (DLI) is used after stem cell transplantation to treat and prevent relapse, to prevent infections and to establish full donor chimerism. However, an expected side effect of the presence of mature T cells is the potential occurrence of acute GVHD (24). Evidence has emerged that escalating DLI has achieved higher clinical response rates with lower GVHD occurrence (25). Optimization of DLI dose and schedule as well as strategies of donor T-cell manipulation may lead to the consistent ability to separate GVHD from GVL activity and improve the safety of DLI treatment. One way to manipulate donor lymphocytes to reduce GVHD is leukemia antigen stimulation, in order to increase antileukemia activity while reducing the number of alloreactive T cells by specific culture.

Somatic cell therapy with anti-leukemia CTLs may offer a new tool to prevent or treat relapse. The major advantage of immune-based therapies is the possibility to use highly selective immune effector cells directed against malignant cells, thus limiting treatment related toxicities.

## Pre-clinical background

Allogeneic or autologous anti-leukemia CTL directed against minor histocompatibility antigens or the BCR/ABL neoantigen (26–29), have been successfully employed to treat relapsed leukemia in adult patients representing proof of principle for the potential efficacy of this form of T cell therapy.

During the last decade, the proponent’s research unit has developed and optimized a procedure to generate donor-derived CTLs directed against pediatric acute LB, through the stimulation of peripheral blood mononuclear cells (PBMC) with IFN-dendritic cells (IFN-DC) pulsed with apoptotic LB as source of tumor antigens. CTLs generated *ex vivo* with this approach are likely to recognize a broader range of TAA, potentially reducing the risk of selecting variant leukemic subclones (30–32). Anti-leukemia CTLs include both effector and memory T-cells, suggesting the presence of lymphocytes able to exert, not only an immediate cytotoxic effector activity, but also to maintain long-term immune surveillance (33).

A major risk with the use of donor-derived anti-leukemia CTL is the subsequent development of GVHD. This risk is particularly relevant in the setting of haplo-HCT, where the donor and recipient are HLA partially-matched. In this regard it has been documented that although some anti-leukemia CTL lines showed sizeable cytotoxicity against patients’ derived PHA-blasts, the vast majority displayed lower levels of alloreactivity compared with that observed against LB, especially at the lowest E:T (31, 32).

Any successful cell therapy approach strongly depends on the possibility to *in vitro* generate a product with a high level of standardization in compliance with GMP. Anti-leukemia CTL are Advanced Therapy Medical products (ATMP) and GMP guidelines ensure their quality and safety in terms of sterility, purity and potency for *in vivo* use. Since 2016, after optimizing protocols for obtaining highly specific anti-leukemia CTL, ATMP have been prepared in the Fondazione IRCCS Policlinico San Matteo’s GMP facility “Cell Factory”.

In a recent paper (34), we reported data obtained in 51 batches of ATMP documenting that biological QC, including cell viability, identity, phenotype and potency were in compliance with the defined cut offs. We also deeply evaluated the phenotypic and functional features of ATMP batches using biological assays, other than those necessary for batch release. By comparing the ability of each ATMP to lyse LB in the cytotoxicity assay and to secrete IFN-γ and TNF-α in response to LB, we documented that the majority of ATMPs displayed sizeable levels of cytotoxic activity against LB and high percentages of cytokine-secreting cells. No significant differences were documented in the potency of ATMP obtained after 1^st^ and the 2^nd^ round of rapid expansion. In few ATMP derived from different donors, unable to mount sizable levels of cytotoxic activity against patients LB, high percentages of IFN-γ and/or TNF-α-secreting cells were documented. These data suggested that anti-leukemia CTL are able to mediate anti-leukemia activity by different mechanisms and that the secretion of cytokines with anti-tumor activity can make up for low levels of direct lytic activity (34).

ATMP were also characterized for surface antigens of terminal differentiation and exhaustion, which can be an indirect sign of impaired function or persistence. The analysis of all batches of ATMP produced so far documented that the majority of cells were CD3+/CD8+ cells, with a memory/terminal activated phenotype including also measurable percentages of T central memory (TCM). Anti-leukemia CTL appear more highly differentiated than exhausted in that we also documented a low percentages of the PD1+/TIM3 population, usually associated with an exhausted phenotype. In donor/recipient pairs in which more than one batch of ATMP was produced, biological QC and additional biological assays documented that they were homogeneous in terms of surface antigens and potency (34).

Altogether these results demonstrated that the methodological approach we have optimized protocol is highly reproducible and allows the generation of large numbers of immunologically safe and functional anti-leukemia CTL with a high level of standardization. Based on their features, anti-leukemia CTLs could be a safe and efficient somatic cell therapy to prevent/treat leukemia relapse in children given haplo-HCT for high-risk acute leukemia.

## Methods and analysis

### Trial design

Leuk-001 is a Phase I/II, monocentric, open label, non-randomized, prospective clinical trial of donor-derived anti-leukemia CTLs in pediatric haplo-HCT recipients transplanted for ALL or AML and with a risk of leukemia relapse after haplo-HCT ≥ 50%. The outcome of treated patients will be compared with that of pediatric recipients of haplo-HCT with the same disease characteristics and prognosis, who received infusions of unmanipulated DLI. Patients will be assigned to the treatment with anti-leukemia CTLs (experimental arm) or to standard treatment with DLI (control arm) based on the availability of cryopreserved viable LB collected at the diagnosis or at relapse, necessary for the production of anti-leukemia CTLs (**Figure 1**). Therefore, this will be the only difference between the study population and the control population.

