### Patients’ selection

Fifteen pediatric subjects will be enrolled in this study after obtaining informed consent. The study population will comprise any infant (1 month- 24 months), child (2–11 years) and teenager (12–18 years) affected by high-risk ALL or AML, candidate to an haplo-HCT and with an expected risk of leukemia relapse after transplantation ≥ 50% according to the available literature data. In **Tables 1**, **2** patients’ inclusion and exclusion criteria are reported, respectively. Eligible donors are HLA haploidentical relatives, including but not limited to biological parents, siblings, or half-siblings. Matching will be determined by class I and class II DNA typing. In **Table 3**, donor inclusion and exclusion criteria are reported.

**Table 1 T1:** Inclusion criteria for ALL and AML patients’ enrolment.

ALL patients’ inclusion criteria	AML patients’ inclusion criteria
Age ≥ 1 month and ≤ 18 years	Age ≥ 1 month and≤ 18 years
Life expectancy > 12 weeks	Life expectancy > 12 weeks
ALL in first morphological remission but with a positive MRD≥ 1 x 10–^3^ before HCT	AML in first morphological remission and with a flow cytometry MRD at the end of induction therapy ≥ 0.1%;
ALL in second morphological remission after a high-risk relapse (patients belonging to the S3-S4 BFM risk group), independently of the level of MRD	AML in first morphological remission and with high-risk disease according to the presence of unfavorable cytogenetic or molecular aberrations
ALL in second morphological remission with any MRD positivity before HCT	AML in first morphological remission after a primary induction failure
ALL in third or subsequent morphological remission, independently of the level of MRD	AML in second morphological remission
ALL patients not in morphological remission at time of HSCT	AML in third or subsequent morphological remission
Pre-HSCT Lansky/Karnofsky score ≥ 40%.	Pre-HSCT Lansky/Karnofsky score ≥ 40%.
HIV negativity	HIV negativity

**Table 2 T2:** Exclusion criteria for patients’ enrolment.

Patients’ exclusion criteria
Ongoing active acute GVHD or chronic GVHD due to a previous allograft
Presence of clinically active infectious disease (including positive HIV serology or viral RNA)
Severe cardiovascular disease (arrhythmias requiring chronic treatment, congestive heart failure or left ventricular ejection fraction <40%)
Liver dysfunction (AST/ALT ≥ 3 times institutional upper limit normal value –ULN- or bilirubin > 3 times ULN)

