### Sample size and data analysis

The sample size is calculated based on the primary safety endpoint, using the single stage method for phase II studies proposed by Fleming (35). This method has been primarily designed to provide sufficient clinical experience to support the design of later-stage clinical development such as phase III studies. We assumed a maximum proportion P0 of patients developing GVHD, for patients receiving the standard treatment (DLI), of 40% based on our previous experience, and on data reported in the literature (H0). We consider 10% as the maximum proportion P1 of patients developing GVHD for the study treatment (CTLs) to consider the study treatment for preliminary success (H1). A sample size of 15 patients (including a dropout of 1 patient) will be able to reject H0 with a power of 80% and a type I error of 5%. If the number of responses at the end of the study is ≤ 2, H0 will be rejected; if the number of responses is > 2, H1 will be rejected. Quantitative variables will be reported as the median value and range, while categorical variables will be expressed as absolute numbers and percentage. The demographic and clinical characteristics of patients and controls will be compared using the Chi-square test or Fisher’s exact test for categorical variables, while the Mann-Whitney rank sum test or the Student’s t-test will be used for continuous variables as appropriate. Overall survival (OS) and event-free survival (EFS) will be calculated according to the Kaplan-Meier method, while the risk of acute and chronic GVHD, relapse and death in remission, defined as non-relapse mortality (NRM) will be calculated as cumulative incidences (CI) in order to adjust the analysis for competing risks. Comparisons between different OS and EFS probabilities will be performed using the Log-Rank test, while the Gray’s test will be used to assess, in univariable analyses, differences between cumulative incidences. All results will be expressed as probabilities (%) or cumulative incidences (%) and 95% confidence interval (95% CI), at 3, 6, 9, 12, 18 and 24 months from HCT. P values < 0.05 will be considered statistically significant. Statistical analysis will be performed using NCSS [NCSS 10 Statistical Software (2015). NCSS, LLC. Kaysville, Utah, ncss.com/software/ncss.] and MP/15 (StataCorp LP, [name] (http://www.stata.com).

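### Assigning patients by stored-blast availability does not make the arms alike, so the unadjusted CTL versus DLI comparisons can carry case-mix bias

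*Protocol article*

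**What the plan says.** The Trial design section describes the study: "Leuk-001 is a Phase I/II, monocentric, open label, non-randomized, prospective clinical trial". Arms are assigned "based on the availability of cryopreserved viable LB collected at the diagnosis or at relapse, necessary for the production of anti-leukemia CTLs". Controls are described as "pediatric recipients of haplo-HCT with the same disease characteristics and prognosis, who received infusions of unmanipulated DLI". The section then concludes: "Therefore, this will be the only difference between the study population and the control population". The Discussion repeats the idea: it frames the primary objective as a comparison with a control cohort whose characteristics it calls identical. No matching or selection step is described in support.

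Table 1, under Patients' selection, sets a wide range. For ALL it runs from "ALL in first morphological remission but with a positive MRD" through second and third or later remission to patients not in remission at transplant. For AML it runs from first remission with an adverse feature to third or later remission. MRD positivity is required in some categories and irrelevant in others. The common condition is an expected relapse risk of at least 50%.

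Under Sample size and data analysis, OS and EFS are compared by the log-rank test, and Gray's test is "used to assess, in univariable analyses, differences between cumulative incidences". P < 0.05 counts as significant. On balance between arms the section says: "The demographic and clinical characteristics of patients and controls will be compared using the Chi-square test" or Fisher's exact test, with rank-sum or t-tests for continuous variables. It attaches no consequence to a difference. The only adjustment named is for competing risks.

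**The concern.** An allocation rule says how patients were sorted. It does not show that the sorted groups are alike. Whether viable blasts were stored, from diagnosis or from relapse, may plausibly go with blast burden, relapse history, referral or calendar period, and any of these may go with outcome. The article shows no such link and gives no direction for it, but it gives no ground for excluding one either.

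At stake is how the comparison with DLI is read. Relapse is the key secondary endpoint, and OS, EFS, NRM and GVHD are also set against the DLI group. If one arm holds more patients who are MRD-positive or not in remission, an unadjusted comparison attributes the resulting difference to treatment. The comparability statements invite readers to accept that attribution.

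**Working it through.** **1. The plan's own figure.** The sample-size section gives 15 patients including one dropout, H0 40%, H1 10%, and rejection of H0 with 2 or fewer GVHD cases. With n = 14 and X binomial:
- type I error = P(X ≤ 2 | 14, 0.40) = 0.040
- power = P(X ≤ 2 | 14, 0.10) = 0.84

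At n = 13 the type I error is 0.058, so 14 plus 1 reproduces the stated size. At n = 15 the values are 0.027 and 0.82. No control patient enters this calculation, so imbalance between arms cannot alter the rule.

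**2. Bias in relapse with no CTL effect.** These inputs are assumptions, since the article gives no stratum-specific rates:
- lower-risk stratum 50%, the eligibility floor
- higher-risk stratum 70%
- higher-risk share 30% in the CTL arm and 60% in the DLI arm

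Expected relapse = share × 0.70 + (1 − share) × 0.50:
- CTL: 0.30 × 0.70 + 0.70 × 0.50 = 0.56
- DLI: 0.60 × 0.70 + 0.40 × 0.50 = 0.62

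The spurious difference is 6 points. It equals the difference in shares times the difference in rates: 0.30 × 0.20 = 0.06.

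Range for other assumptions at or above the 50% floor:

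| Higher-risk share, CTL v DLI | Relapse 50% / 70% by stratum | Relapse 50% / 80% by stratum |
|---|---|---|
| 30% v 50% | 4 points | 6 points |
| 30% v 70% | 8 points | 12 points |
| 20% v 80% | 12 points | 18 points |

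With the imbalance reversed (70% v 30%), the bias is 8 or 12 points against CTL.

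**3. Would the planned baseline tests reveal it?** Exact power of Fisher's test at two-sided 5% for 30% v 60% higher-risk patients, with 15 CTL patients (the control number is not stated, so it is varied):
- 15 controls: 0.227
- 30 controls: 0.39
- 60 controls: 0.54

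At 15 v 15 the imbalance is missed about three times in four. For 30% v 50% the power is 10%, 18% and 26%.

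**4. Would the bias produce a significant result?** Fisher's test on 56% v 62% at 15 v 15, as a simple stand-in for Gray's test, favours CTL significantly 1.9% of the time, so rarely. A two-proportion test across the table above, with 15, 30 or 60 controls, gives 3.9% to 29.4%, against a nominal 2.5% in that direction. The upper end needs the most extreme imbalance (20% v 80%) and 60 controls.

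**5. The between-arm GVHD comparison.** Relapse is a competing event for GVHD (Study objectives), so relapse risk also moves GVHD incidence. Assume constant hazards g (GVHD) and c (competing events) and a net GVHD risk of 40% at 6 months. Cumulative incidence = g/(g + c) × [1 − exp(−(g + c) × 6)]. It is 36%, 32% and 27% for net competing risks of 20%, 40% and 60%. An arm with more relapse would show less GVHD without being safer.

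**The case against.** The strongest reply is that the formal decision does not use the controls. The 2-or-fewer rule is single-arm, Study objectives defines the primary endpoint as an incidence, and only the Discussion turns it into a comparison. All of this stands. A reader might infer that imbalance undermines the primary safety conclusion; the sample-size section does not support that.

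A reader might also infer that blast availability is known to be prognostic, or to favour CTL. The article shows neither. Nor does it say that a patient with stored blasts but no released product leaves the study or moves to DLI: assignment is by blast availability, and the pre-clinical section reports 51 batches whose biological quality controls met the cut-offs. The point does not rest on such a crossover.

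On size, a lower-risk relapse rate below 50% would contradict the eligibility floor, and within the floor the central illustration is modest. It biases the estimate more than it produces false significance.

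Finally, an analysis plan not shown here may add stratified analyses, baseline comparison is planned, and relapse is already called preliminary efficacy. That softens the point but does not answer it. The article affirmatively states that the arms do not otherwise differ, and it names univariable tests with a significance threshold. The baseline tests detect little at this size and trigger nothing. Whether baseline balance is reported by P values or standardized differences is a matter of style and carries no weight here.

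**Conclusion.** The concern holds for the between-arm comparisons of relapse, OS, EFS, NRM and GVHD. The statements that the arms differ only in blast availability, and that controls have identical characteristics, are unsupported, and the unadjusted tests named give no protection if they are wrong. The primary single-arm GVHD rule and the sample size of 15 stand.

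The central illustration is a 6-point spurious relapse difference (56% v 62%), with a 23% chance that the baseline test flags the imbalance behind it. It rests on assumed stratum rates, assumed risk shares and, for the 23%, an assumed 15 controls. Other assumptions within the eligibility floor give 4 to 18 points when CTL patients are at lower risk, and bias against CTL when they are at higher risk. The true size and direction cannot be known from the article. The conclusion is that case mix can bias these comparisons, not that it will create a false CTL benefit.

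**What to change.** - Delete the only-difference sentence in Trial design and the identical-characteristics description in the Discussion. The Trial design wording that controls share the same disease characteristics and prognosis should then read as an intention, not a fact.
- State that between-arm comparisons are exploratory and non-randomized, and cannot by themselves support a CTL effect.
- State that groups are analysed as assigned by blast availability.
- Keep the univariable tests and add Gray's and log-rank analyses stratified by one pre-stated binary baseline factor: in remission and MRD-negative, versus MRD-positive or not in remission. Remission status is an eligibility item, and marrow MRD is scheduled at baseline under Study procedures.

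The cost is wording and one extra analysis, with no new data and no change to the sample size. Precision falls slightly with few patients per stratum. Residual confounding by disease type and remission number remains, because about 15 CTL patients cannot support fuller adjustment; that is why the exploratory label is needed as well as the stratified test.
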